### Interventions

Both types of interventions will last 1 year.

#### Self-Rehabilitation

Patients allocated to this group will undergo an intensive self-rehabilitation protocol based on the principles of “Guided Self-Rehabilitation Contract” (11, 12). This approach consists of an antagonist-targeting self-rehabilitation treatment supported by a diary and based on a moral contract between patient and therapist. In particular, therapists will define, teach, and readjust over time a daily program of self-stretch postures and training exercises according to the needs and progress of each patient. Furthermore, the therapist will provide each patient with an illustrated manual that describes the training program. The stretching program involves static postures of stretching at a high load below the pain threshold for specific antagonist muscle groups; tension on the stretched muscles should be kept for a cumulative period of ≥10 min a day per targeted muscle. The training program includes a series of unassisted rapid alternating movements (or movement efforts) of possible maximum amplitude against targeted antagonist muscles in a short time (e.g., 15–30 s per series, depending on fatigability). At each visit a diary will be requested from the patient reporting the actual practice of self-treatment (e.g., daily time, number of repetitions).

#### Usual Rehabilitation Care

In this group, physiotherapy sessions will be freely prescribed by the patient's physiatrist, according to the usual care practice, which take into account not only medical opinions but also the patient's needs and requests. This community-based therapy sessions are universally and indefinitely covered by the public National Health System in Italy. Physiotherapists providing rehabilitation sessions in this group will be freely selected by the patient and/or recommended by the physiatrist, as in routine practice.

### Outcomes

The primary endpoint of WP1 is comparison of sensorimotor disability after self-rehabilitation vs. usual care treatment. Accordingly, its primary outcome is Fugl-Meyer assessment (FMA), which comprises five domains (155 items in total) as follows: motor function of the upper and lower extremities; sensation, tested through a light touch on two surfaces of the arm and leg, as well as position sense for eight joints; balance, three seated and four standing tests; joint range of motion, testing eight joints; and joint pain. Items are scored on the basis of ability to complete the item, according to which 0 = cannot perform; 1 = performs partially; and 2 = performs fully. The maximum total scale score is 226. Points are divided among the domains as follows: the motor function score ranges from 0 (hemiplegia) to 100 points (normal motor performance) and is divided into 66 points for the upper extremities and 34 points for the lower extremities; the sensation score ranges from 0 to 24 points and is divided into 8 points for light touch and 16 points for position sense; the balance score ranges from 0 to 14 points and is divided into 6 points for sitting and 8 points for standing; the joint range of motion and pain scores range from 0 to 44 points (13).

The secondary endpoint of WP1 is comparison of cognitive and global disability after self-rehabilitation vs. usual care treatment. Accordingly, its secondary outcomes are the Cognitive Oxford Screen (OCS) and the Barthel Index (BI). The OCS is structured on five cognitive domains (namely, attention and executive function, language, memory, number processing, and praxis) and consists of 12 tasks as follows: picture naming (score range 0–4); semantics (score range 0–3); orientation (score range 0–4); visual field (score range 0–4); sentence reading (score range 0–15); number writing (score range 0–3); calculation (range score 0–4); broken hearts (range score 0–50); imitation (range score 0–12); recall and recognition (range score 0–4 each); and executive task (range score 0–13). The cutoffs are adjusted for age, gender, and years of education (14). The BI measures the extent to which somebody can function independently and has mobility in their activities of daily living (i.e., feeding, bathing, grooming, dressing, bowel control, bladder control, toileting, chair transfer, ambulation, and stair climbing). The score ranges from 0 to 100 (15). Other factors considered in the WP1 will be structural and functional neuroimaging, cortical excitability, motor, and somatosensory evoked potentials.

Evaluation endpoints of WP2 include the ability to process visual-spatial information consciously or unconsciously by means of reaction times and to allocate selective attention to the environment around the patient; the ability to perceive relevant elements for behavioral attitudes by means of eye movements and to transform sensory information into appropriate movements, in both a reactive and a predictive way. Accordingly, the outcomes include behavioral measures—e.g., reaction times, eye movements and limb movements—and instrumental measures—e.g., cortical excitability and cortical connectivity—assessed by means of paired transcranial magnetic stimulation and electroencephalographic phase synchrony.

The evaluation endpoints of WP3 include the measurements of fatigue, body composition, and gait. Accordingly, the outcomes include the Multidimensional Fatigue Inventory, which aims to measure the frequency and severity of global fatigue, with a score ranging from 0 to 100, and to define the type of physical/muscular and mental fatigue (16). Other measures include body densitometry (DEXA), walking energetics, and mechanics.

Evaluation endpoints of WP4 include incidence of psychopathology (e.g., anxiety and depression) after stroke and related pain conditions, psychopathological issues, and coping strategies affecting adherence to rehabilitation programs, effectiveness of psychopharmacological and psychotherapeutic treatments in stroke patients, definition of specific psychological interventions supporting rehabilitation (17, 18). Accordingly, the outcomes considered are the Symptom Checklist-90 scale (19); the Eysenck Personality Questionnaire-R (20); the COPE scale (21); the General Self-Efficacy Scale (22); the Acceptance and Action Questionnaire-II scale (23); the Multidimensional Scale of Perceived Social Support (24); the Brief Pain Inventory-I scale (25).

The main endpoint of WP5 is to evaluate changes in microbiota related to post-stroke condition and recovery. Accordingly, the gut microbiota (GM) composition and changes will be evaluated at different time points. To identify bacterial species, present in GM, analysis of nine variable regions of 16S ribosomal RNA gene will be performed by next generation sequencing (NGS). Bioinformatical and statistical analyses will be conducted to relate gut microbiota signatures at different taxonomic levels to stroke rehabilitation conditions (25).

The main endpoint of WP6 is to evaluate the expression of microRNAs (miRNAs) related to post-stroke condition and recovery. Accordingly, in this study, the expression levels of circulating miRNAs (miR-9; miR-29a- 3p; miR-155-5p; miR-124; miR-146a; miR-210; miR-371-3p; miR-495-3p; miR-941; spike-in) will be analyzed at different time points starting from serum samples.

The main endpoint of WP7 is to evaluate the relationship between stroke, oxidative stress, and neuronal death issues. Accordingly, the following concentrations will be analyzed at different time points starting from plasma samples: glutathione disulphide ratio [GSH]/[GSSG]; nitrite/nitrate ratio [NO2^−^]/[NO3^−^]; and post-translational oxidative modifications of plasma proteins. Furthermore, the activation of STAT1 signaling will be evaluated in Peripheral Blood Mononuclear Cells (PBMC).

Evaluation time points for all WPs are reported in Table 1.

**Table 1 T1:** Evaluation time points.

	**T0°**	**T1°**	**T2°**	**T3°**	**T4°**
	**First week**	**3 months**	**6 months**	**9 months**	**12 months**
Informed consent	✓				
Inclusion and exclusion criteria	✓				
Clinical history	✓				
Fugl-Meyer Assessment	✓	✓	✓	✓	✓
Oxford Cognitive Screen	✓	✓	✓	✓	✓
Barthel Index	✓	✓	✓	✓	✓
Volumetric analysis of the stroke	✓				
Side and site of stroke	✓				
DTI	✓				
fMRI	✓				✓
MEP and cortical excitability to TMS	✓				✓
SSEP	✓				✓
EEG	✓		✓		
MFI	✓		✓		
DEXA			✓		
Microbiota			✓		
Biochemistry and miRNA analysis	✓				✓
Usual care	✓	✓	✓	✓	✓
Intensive self-rehabilitation program	✓	✓	✓	✓	✓
Physiatric evaluation	✓	✓	✓	✓	✓
Video analysis and energetic cost of the gait	✓	✓	✓	✓	✓
Psychological evaluation scales	✓	✓	✓	✓	✓
Informed consent	✓	✓	✓	✓	✓

*DTI, Diffusion Tensor Imaging; fMRI, functional Magnetic Resonance Image; MEP, Motor evoked potential; SEP, Somatosensory evoked potential; TMS, Transcranial Magnetic Stimulation; EEG, Electroencephalography; MFI, Multidimensional Fatigue Inventory; DEXA, Dual X-ray Absorptiometry; miRNA, microRNA. °Time from the enrollment*.

### Sample Size

We estimated that 88 subjects, 44 patients per group, would provide 80% power (α level 5%) to detect a difference of 7 points (SD 11.6) on the FMA, the primary outcome, between the groups (26). Considering a dropout rate of 10%, we planned to enroll a total of 97 patients in this study.

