## Abstract

**Background:** Stroke is a leading cause of disability. Nonetheless, the care pathway for stroke rehabilitation takes partially into account the needs of chronic patients. This is due in part to the lack of evidence about the mechanisms of recovery after stroke, together with the poor knowledge of related and influencing factors. Here we report on the study protocol “Rehabilitation and Biomarkers of Stroke Recovery,” which consists of 7 work-packages and mainly aim to investigate the effects of long-term neurorehabilitation on stroke patients and to define a related profile of (clinical-biological, imaging, neurophysiological, and genetic-molecular) biomarkers of long-term recovery after stroke. The work-package 1 will represent the main part of this protocol and aims to compare the long-term effects of intensive self-rehabilitation vs. usual (rehabilitation) care for stroke.

**Methods:** We planned to include a total of 134 adult subacute stroke patients (no more than 3 months since onset) suffering from multidomain disability as a consequence of first-ever unilateral ischemic stroke. Eligible participants will be randomly assigned to one of the following groups: intensive self-rehabilitation (based on the principles of “Guided Self-Rehabilitation Contract”) vs. usual care (routine practice). Treatment will last 1 year, and patients will be evaluated every 3 months according to their clinical presentation. The following outcomes will be considered in the main work-package: Fugl-Meyer assessment, Cognitive Oxford Screen Barthel Index, structural and functional neuroimaging, cortical excitability, and motor and somatosensory evoked potentials.

**Discussion:** This trial will deal with the effects of an intensive self-management rehabilitation protocol and a related set of biomarkers. It will also investigate the role of training intensity on long-term recovery after stroke. In addition, it will define a set of biomarkers related to post-stroke recovery and neurorehabilitation outcome in order to detect patients with greater potential and define long-term individualized rehabilitation programs.

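### The Abstract plans 134 randomised patients and the Sample Size section plans 97; nothing in the article reconciles the two totals

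*Protocol article*

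**What the plan says.** The Abstract (Methods) states: "We planned to include a total of 134 adult subacute stroke patients". Its next sentence begins "Eligible participants will be randomly assigned to one of the following groups" and names the two arms, so the 134 refers to the randomised population.

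The Sample Size section takes 88 subjects, 44 per group, as sufficient for 80% power at a 5% level "to detect a difference of 7 points (SD 11.6) on the FMA, the primary outcome, between the groups". It then adds dropout: "Considering a dropout rate of 10%, we planned to enroll a total of 97 patients in this study".

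The section on randomisation gives a 1:1 ratio under a restricted, software-generated scheme. The Participants section adds eligibility criteria for work packages 2, 3 and 4. No section mentions 134 again or assigns it to a different population.

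**The concern.** Both figures are presented as the planned total for one trial, and they cannot both be right. The gap is 134 − 97 = 37 patients, or 38% of 97.

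The total is what tells the team, the ethics committee and later readers when recruitment is complete. The Discussion itself names the number of patients enrolling, at a single centre, as a possible main problem, so where recruitment ends is a practical question here. With two published totals, a final count near either one could be described as the planned number, and a reader of the results could not tell whether the trial fell short of its target, met it or exceeded it.

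The power for which the trial was sized is also ambiguous, because the two totals correspond to different power under the stated effect, SD and dropout.

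**Working it through.** **Inputs** (Sample Size section unless noted): difference 7 points; SD 11.6; α 5%; power 80%; 10% dropout; 1:1 allocation (randomisation section); totals 97 (Sample Size) and 134 (Abstract). The article does not say whether α is one- or two-sided. Two-sided is assumed because it reproduces the stated 44 per group; one-sided gives 34.

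**1. Reproduce the 88.** Normal approximation: n per arm = 2 × (1.960 + 0.842)² × (11.6/7)² = 2 × 7.85 × 2.746 = 43.1, rounded up to 44, so 88 in total. The two-sample t-test version gives 44.09 per arm, and power at exactly 44 per arm is 79.9%. The stated 88 reproduces.

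**2. Reproduce the 97.** Two routes lead to it:
- 88 × 1.10 = 96.8, rounded to 97.
- 88/(1 − 0.10) = 97.8, truncated to 97. Rounded up, this is 98.

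Checking backwards, 97 × 0.90 = 87.3, just short of 88, while 98 × 0.90 = 88.2.

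**3. Try to reproduce the 134.**
- From 88 evaluable, the implied dropout is 1 − 88/134 = 34.3%, against the stated 10%.
- At 90% power the t-test needs 59 per arm, 118 in total; 118/0.90 = 131.1. By normal approximation it is 58 per arm, 116 in total; 116/0.90 = 128.9.
- At 95% power (normal approximation) it is 72 per arm, 144 in total; 144/0.90 = 160.

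None of these gives 134.

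**4. Power after 10% dropout, for 7 points and SD 11.6, two-sided 5%.**

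| Enrolled | Evaluable | Per arm | Power (t-test) | Power (normal approx.) |
|---|---|---|---|---|
| 97 | 87.3 | 43.65 | 79.6% | 80.5% |
| 98 | 88.2 | 44.1 | 80.0% | 80.9% |
| 134 | 120.6 | 60.3 | 90.8% | 91.2% |

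The contradiction between 97 and 134 is worth about 11 percentage points of power (90.8 − 79.6 = 11.2). The step from 97 to 98 is worth about 0.4.

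**The case against.** The strongest defence is that the Sample Size section is where the target is derived, that 97 follows from its inputs, and that 134 appears once, without support, in the Abstract. On that view 134 is a figure left uncorrected and the working target is 97. This may well be so, but the article does not show it. The 134 is stated as planned, is tied directly to randomisation, and is the number most readers will see first. Nor do the extra work-package criteria explain it, because they narrow the population and cannot produce a larger total. This is also not a detail that an article leaves to the full protocol, since both numbers are printed and they disagree.

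The defence is right to limit what follows from the contradiction. A reader might infer four stronger things that the article does not support:

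- *That the trial's power is undefined.* The Sample Size section fixes 80% on 88 evaluable patients, and that calculation reproduces. Both totals reach that level, or come within half a point of it, at the stated dropout.
- *That dropout was inflated by the wrong formula.* No formula is shown, and truncating 88/0.90 gives 97 as readily as rounding 88 × 1.10. The shortfall is one patient, well inside the uncertainty of a 10% planning guess.
- *That an odd total cannot be randomised 1:1.* A 49/48 split is ordinary under restricted randomisation.
- *That type I error is inflated.* Testing at about 88 and again at about 120 evaluable patients, each at 5%, would give about 7.4%. But this requires a look at unblinded results followed by a results-driven decision to continue, and the Data Analysis section plans no interim look.

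**Conclusion.** The concern holds as an internal contradiction. The planned total is 134 in one place and 97 in another, for the same randomised trial, and the article offers no way to choose between them. The size is 37 patients, with about 80% power at 97 and about 91% at 134. These figures assume a two-sided 5% test, 10% dropout spread evenly over the arms, and the stated 7 points and SD 11.6.

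The 88 evaluable patients are correctly derived and 134 cannot be obtained from the stated inputs. It does not follow that the Abstract is the place in error, because 134 could be an approved target whose derivation was not carried into the article. Only the sponsor can settle that.

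The difference between 97 and 98 is a rounding remark and would not merit a point by itself.

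**What to change.** State one total in both the Abstract and the Sample Size section.

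- **If the Sample Size derivation stands:** correct the Abstract to that figure. In the same edit, write 98 (49 per arm) in place of 97, so that 10% dropout leaves 88.2 rather than 87.3 evaluable patients.
- **If 134 is the approved target:** rewrite the Sample Size section with the assumptions that lead to it and the power it gives. With the present effect, SD and dropout, that is about 60 per arm evaluable and about 91%.

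In either case, say that α is two-sided, since the 44 per group depends on it.

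The cost is a wording change in two places, plus a check that the randomisation list covers the chosen total. Under the first option the target rises by one patient above 97. The analysis does not change under either option.

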### Data Analysis

Adequate descriptive statistics will be produced, including frequency, mean, median, standard deviation, interquartile range, and confidence intervals, for the demographic data and outcome measures at each time point. As to WP1, the comparison between groups, in terms of self-rehabilitation vs. usual care, with regard to the outcomes considered at each time point of the various evaluation times, will be performed using parametric (e.g., *t*-test, ANOVA) and/or non-parametric statistics, such as the Kruskal-Wallis test or the Mann-Whitney test, depending on the data distribution. Correlation and regression analyses will also be performed between neuroimaging data, neurophysiological variables, and clinical outcomes at different time points. As to the other WPs (2–7), comparisons between groups at different times will be assessed using parametric tests, such as the Student *t*-test and ANOVA, or non-parametric tests, such as the Kruskal-Wallis test and Mann-Whitney test, depending on the data distribution. For each variable considered, both longitudinally and transversely, correlation and regression analyses will also be performed. Moreover, for each WP we will perform longitudinal intragroup comparisons at different times by means of parametric tests, such as the *t*-test and ANOVA and/or non-parametric tests, such as the Friedman test and the Wilcoxon test, depending on data distribution. The statistical analysis will be performed using the Statistical Package for Social Science SPSS® version 26.0 software for Macintosh (SPSS Inc., Chicago, IL, USA). For all statistical tests, the significance level is set at *p* < 0.05.

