### Randomization, Allocation Concealment, and Blinding

Prior to testing, eligible participants are randomly assigned in a 1:1 ratio to one of the two interventions of WP1: intensive self-rehabilitation (Group 1) vs. usual rehabilitation care (Group 2). The patients will be allocated to one of the two intervention arms according to a balanced (restricted) software-generated randomization scheme. Once the decision has been made, the investigator, who has determined whether a subject is eligible for the trial, is unaware of which group the subject would be allocated to (with the allocation contained in opaque sealed envelopes). Another investigator will check for correct patient allocation according to the randomization list. Investigators who assess outcomes are blinded to the intervention performed.

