## Discussion

This trial will evaluate and follow up stroke patients from subacute stroke to the chronic phase, up to 1 year after stroke onset. It will deal with the effects of an intensive self-management rehabilitation protocol and a related set of biomarkers. In our view it will add some important pieces of evidence to overcome current conceptual limitations on long-term recovery models, upon which the usual care pathway of stroke rehabilitation is based. Another aspect that will be investigated by this study is the role of training intensity on long-term recovery after stroke, a point that will be further strengthened by the moral contract between patients and therapists (12). As suggested in the literature, intensity is a key element of stroke rehabilitation in order to achieve greater training effects (2, 27). In addition, a pattern of biomarkers related to post-stroke recovery and neurorehabilitation outcome will be useful to detect those patients with greater potential for recovery. Despite the fact that some of these biomarkers have been previously reported to offer information on stroke rehabilitation outcome, the prognostic relevance of their combination has never been explored to date and may be important for defining future long-term personalized medical rehabilitation programs. The possible main problems concerning the conduct of the study will be the number of patients enrolling, this being a single center study, the long follow-up duration (1 year), and the multifactorial/multimodal approach to evaluate patients; (that is, many different outcomes will be considered).

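### The arms are compared on the FMA one visit at a time, so by default a patient who leaves before 12 months contributes nothing to the 12-month comparison; this could bias it if dropout, or its link to recovery, differs by arm.

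*Protocol article*

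**What the plan says.** All references are to the protocol article.

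- **Data Analysis.** For WP1 the comparison between groups, "with regard to the outcomes considered at each time point of the various evaluation times, will be performed using parametric" and/or non-parametric tests, is chosen by the data distribution. The between-arm examples are the t-test, ANOVA, Kruskal-Wallis and Mann-Whitney tests. The Friedman and Wilcoxon tests appear later, for comparisons within a group over time.
- **Table 1.** The FMA is scheduled at T0 and at 3, 6, 9 and 12 months, timed from enrolment.
- **Sample Size.** The trial is sized at 44 per arm, 88 in all, with power of 80% at a 5% level, "to detect a difference of 7 points (SD 11.6) on the FMA, the primary outcome, between the groups". The allowance for attrition is given next: "Considering a dropout rate of 10%, we planned to enroll a total of 97 patients in this study".
- **Randomization.** "eligible participants are randomly assigned in a 1:1 ratio to one of the two interventions of WP1".
- **Self-Rehabilitation.** This arm has a daily programme, a moral contract with the therapist, and a diary: "At each visit a diary will be requested from the patient reporting the actual practice of self-treatment". The section on usual care describes none of these.
- **Discussion.** Among the possible main problems of conduct it lists "the long follow-up duration (1 year").

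The article states no complete-case or per-protocol rule, and gives no dropout rate or reason for leaving by arm.

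**The concern.** A two-sample test at 12 months needs a 12-month value. Unless missing values are filled in first, a patient assessed at T0, 3 and 6 months who then leaves is absent from the 12-month comparison, although three FMA scores are on file. The patients analysed may then also differ from visit to visit.

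This does no harm if those who leave resemble each other in both arms and leave at the same rate. It can do harm if they do not. A difference is plausible here because only one arm is asked to keep up a daily programme and account for it in a diary at each visit. That is an inference from the design; the article does not say it.

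At stake is the primary comparison. If poor recoverers were lost mainly from one arm, the observed 12-month means would no longer compare the groups that were randomised.

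**Working it through.** **1. The plan's own figure.** Inputs from Sample Size: difference 7, SD 11.6, α 5% (two-sided reproduces the figure; one-sided gives 34 per arm), power 80%.

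- n per arm = 2 × (1.96 + 0.842)² × (11.6/7)², which rounds up to 44, so 88 in total. This reproduces.
- Dropout: 88 × 1.10 = 96.8, so 97. Dividing instead gives 88/0.90 = 97.8, so 98. The difference is immaterial.
- Expected completers: 97 × 0.9 = 87.3, with power 0.805. Loss of power is not the issue.

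**2. Bias of a completers-only difference.** Let d be the share of an arm that drops out, and g the mean 12-month FMA of its completers minus that of its dropouts. Completers' mean minus the full-arm mean is d × g, so

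bias = d_self × g_self − d_usual × g_usual.

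Neither d by arm nor g is in the article; both are assumed. Take 97 enrolled (48.5 per arm), the same g in both arms, no true effect, and SE = 11.6 × √(1/n_self + 1/n_usual) with n = 48.5 × (1 − d).

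| Dropout, self / usual | g | Bias (points) | Share of 7 | Type I error |
|---|---|---|---|---|
| 10% / 10% | any | 0 | 0% | 5.0% |
| 15% / 5% | 5.8 (0.5 SD) | 0.10 × 5.8 = 0.58 | 8% | 5.6% |
| 15% / 5% | 11.6 (1 SD) | 0.10 × 11.6 = 1.16 | 17% | 7.5% |
| 20% / 0% | 5.8 | 0.20 × 5.8 = 1.16 | 17% | 7.5% |
| 20% / 0% | 11.6 | 0.20 × 11.6 = 2.32 | 33% | 15.3% |

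If g = 0 there is no bias at any split. The bias in points does not depend on the number enrolled.

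**3. Simulation.** Assumptions: 48 per arm, five visits, SD 11.6, correlation 0.7 between visits, no true effect, dropout after the 6-month visit driven by a noisy 6-month FMA. Overall dropout is 10% in every row.

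| Who leaves because of a low FMA | 10% / 10% | 15% / 5% | 20% / 0% |
|---|---|---|---|
| Same mechanism in both arms | about 0 (near 5%) | 0.7 to 1.3 (6% to 9%) | as in the rows below |
| Self-rehabilitation only, weak link | 0.7 (6.4%) | 1.0 (7.1%) | 1.3 (8.2%) |
| Self-rehabilitation only, strong link | 1.3 to 1.4 (8.5% to 9.4%) | 1.9 to 2.0 (13% to 14%) | 2.5 to 2.7 (18% to 20%) |

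Entries are bias in points, with type I error in brackets.

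**4. How extreme is the last row?** If exactly the lowest fraction d at 6 months left one arm, and dropout in the other arm were random, the bias would be φ(z_d)/(1 − d) × 0.7 × 11.6:

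- d = 10%: 0.1755/0.90 × 8.12 = 1.58
- d = 15%: 0.2332/0.85 × 8.12 = 2.23
- d = 20%: 0.2800/0.80 × 8.12 = 2.84

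The strong-link row is therefore close to the most that these assumptions allow. At 10%, a bias of 1.44 means a completer-dropout gap of 1.44/0.10 = 14.4 points, or 14.4/11.6 = 1.24 SD.

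**5. Using the scores on file.** An estimator that also uses the T0 to 6-month scores of all randomised patients had a bias below 0.1 points in every scenario. This is expected, because dropout was generated from an observed score. It shows what the remedy does under missing at random and says nothing about dropout that depends on unseen scores.

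**The case against.** The strongest reply is that much of this is silence. The tests are introduced as examples, a t-test can follow imputation, and the analysis set and missing-data rule commonly stand in a full protocol or SAP that is not shown. That is fair, and the lack of such a rule is not the point here. What stands is that the article does name the between-arm method, visit by visit, for an outcome measured five times. An SAP that follows it takes over the observed-case default unless it adds a step.

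Several stronger readings are tempting, and the article does not support them:

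- **That the result will favour self-rehabilitation.** No dropout by arm or cause is given. Usual-care patients may also leave after poor recovery, and recovered patients may leave either arm. The Discussion names long follow-up as a general difficulty, without mentioning attrition or arm.
- **That the 10% allowance shows dropouts' data will be discarded.** Such an allowance is routine whatever the analysis.
- **That patients who stop the programme are no longer assessed.** Table 1 times the FMA from enrolment and does not tie it to adherence. Nothing treats a missing diary as withdrawal.
- **That the Friedman and Wilcoxon tests weaken the primary comparison.** They are named for comparisons within a group.

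It is also fair to say that the larger simulated biases come from making dropout depend strongly on the FMA in one arm only. With equal rates and the same mechanism the bias is about 0.

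**Conclusion.** The point holds as a conditional weakness of a stated method. Tests at each visit by default leave a patient without a 12-month FMA out of the 12-month comparison, and between-arm information already collected goes unused. Whether this biases the trial depends on dropout that the article does not describe.

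At the planned 10% overall, and under the simulation's assumptions, the bias is about 0 with equal rates and mechanism, about 0.7 to 2.0 points at 15%/5%, and about 2.7 points in the extreme 20%/0% split. Against the planned 7 points, the last is 2.7/7 = 39%. Type I error runs from 5% to about 20%. The simpler calculation with an equal completer-dropout gap gives 0 to 2.32 points. The correlation, the split by arm and the dropout mechanism are all assumed. Twelve months is taken as the main time point because treatment lasts 1 year. The direction cannot be known in advance.

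The change is worth making because it costs little.

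**What to change.** In Data Analysis, make the primary between-arm analysis of the FMA one likelihood-based mixed model for repeated measures. It should use all scores from T0 to T4 of all randomised patients in their assigned arm, with arm, visit and their interaction, and the 12-month arm contrast should be estimated from it. Comparisons at the other visits can come from the same model.

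Add a sensitivity analysis for data missing not at random, for example shifting missing 12-month scores progressively, separately by arm, until the conclusion changes.

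As a clarification only, add a sentence confirming that Table 1 assessments continue whether or not the patient keeps to the programme. This is best settled before follow-up, since a missed FMA cannot be recovered.

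The cost is a few sentences and a little more analysis work. No extra patients or visits are needed, and SPSS 26, already named, can fit the model. The downside is reliance on a missing-at-random assumption, which the sensitivity analysis is there to probe.

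### No visit is named as primary for the Fugl-Meyer comparison: arms are tested at every visit at p < 0.05, while the sample size assumes one test at 5%

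*Protocol article*

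**What the plan says.** Four parts of the protocol article bear on this.

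- **Outcomes.** The endpoint is worded as "The primary endpoint of WP1 is comparison of sensorimotor disability after self-rehabilitation vs. usual care treatment", with the FMA as primary outcome. No visit is given.
- **Table 1.** The FMA is ticked at T0 and at 3, 6, 9 and 12 months, so there are four post-baseline measurements.
- **Sample Size.** The 88 patients, 44 per group, "would provide 80% power (α level 5%) to detect a difference of 7 points (SD 11.6) on the FMA". Again no visit is given.
- **Data Analysis.** The WP1 arms are compared "with regard to the outcomes considered at each time point of the various evaluation times", by parametric or non-parametric tests. On the threshold: "For all statistical tests, the significance level is set at" p < 0.05.

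The nearest hint of a primary time is in the Interventions section: "Both types of interventions will last 1 year".

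**The concern.** The two statistical sections describe different trials. The Sample Size section describes one comparison of FMA at 5%. The Data Analysis section describes a comparison at every visit, each at 5%, with the visits on an equal footing. Nothing in the article ranks them.

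At stake is the error rate attached to the primary claim. With no visit designated, a difference at 3 months alone, or at 9 months alone, could be presented as the primary result without departing from the written plan. The 5% behind the stated power would then not be the actual risk of a false positive claim. A visit chosen after the data are in would offer no protection either.

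**Working it through.** **Inputs from the article.** Difference 7 points, SD 11.6, α 5%, power 80%, 44 per group (Sample Size); 1:1 allocation (Randomization section); four post-baseline FMA visits (Table 1); p < 0.05 per test (Data Analysis).

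**Assumptions.** Tests are two-sided, since sidedness is not stated. Correlations between the visit-wise test statistics are varied, since the article gives none.

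**Step 1: reproduce the stated sample size.** For one two-group comparison of means,

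n per group = 2 × (1.960 + 0.842)² × 11.6² / 7² = 2 × 7.849 × 134.56 / 49 = 43.1, rounded up to 44.

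This agrees with the article. Power at 44 per group is 0.808 by the normal approximation and 0.799 by the noncentral t distribution. The planned 97 is 88 × 1.1 = 96.8, rounded up. The stated figure therefore corresponds to exactly one two-sided test at 5%.

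**Step 2: error rate over four visits.** Suppose there is no true difference at any visit and significance at any one of the four is taken as support. If the tests were independent, the chance of at least one false positive would be 1 − 0.95⁴ = 18.5%. Repeated scores in the same patients are correlated, so this is an upper reference. Simulation of four correlated normal test statistics (1,000,000 draws each), estimating the probability that at least one exceeds 1.96 in absolute value, gives:

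| Assumed inter-visit correlation | Equal correlation between all visits | Correlation decaying with time, AR(1) |
|---|---|---|
| 0.5 | 15.6% | 16.6% |
| 0.7 | 13.0% | 14.3% |
| 0.8 | 11.4% | 12.7% |
| 0.9 | 9.4% | 10.3% |
| 0.95 | 8.0% | 8.7% |

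T0 is left out because a baseline difference cannot support a treatment claim.

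**Step 3: what each repair implies.**

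- *One designated visit.* One test at 0.05 keeps the primary error rate at 5%, and the 44 per group from step 1 stands.
- *All four visits kept as primary, with Bonferroni.* Each test uses 0.05 / 4 = 0.0125. Then n per group = 2 × (2.498 + 0.842)² × 134.56 / 49 = 61.3, rounded up to 62. That is 124 evaluable, and 124 / 0.9 = 137.8, or 138 enrolled. With 44 per group, power at each visit would be 63%.

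The stated size therefore fits the first option and not the second.

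**The case against.** **The wording points to 12 months.** An endpoint measured after treatment, a treatment lasting one year, a stated interest in long-term effects and a sample size for one comparison all suggest T4. This is a fair reading and probably the intended one, but it remains an inference. The section that governs the tests treats all visits alike.

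**No success rule is stated.** The article never says that significance at any visit establishes efficacy. This stands, and it makes the figures in step 2 conditional: they describe what happens if the plan is read that way, which its text permits.

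**A statistical analysis plan may settle it.** It may. But the article is not merely silent: it fixes testing at each time point and one threshold for every test, so a later document would have to narrow a published rule.

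**A stronger reading is tempting and is not supported.** A reader might infer that error rates far exceed 5% throughout, and that the biomarker set would be filled largely by chance.

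- For the FMA alone, 9% to 16% is roughly two to three times nominal. Each single test still keeps its 5%.
- Multiplying out the 12 tasks of the Oxford Cognitive Screen (OCS) by visit assumes that each task is tested separately between arms. The article names the OCS as one secondary outcome and does not say so.
- The number of biomarker tests is not given, and the share of chance findings depends on how many true associations exist, which is unknown. In Table 1, microbiota is ticked only at 6 months and miRNA only at baseline and 12 months, so these are not tested over four post-baseline visits.
- The article separates primary from secondary outcomes, and the Introduction describes several work packages in exploratory or descriptive terms. Formal adjustment there is a matter of preference; a clear label is enough.

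**Conclusion.** The point holds for the primary outcome. The article prescribes FMA comparisons at every visit at p < 0.05 and designates none as primary, which does not match a sample size built on one test at 5%. If any of the four post-baseline visits may carry the claim, the family-wise error is about 9% to 16% instead of 5%. This rests on two-sided tests, on equal inter-visit correlations of 0.9 to 0.5, and on a reading of the plan that its text allows but does not state. A decaying correlation pattern moves the figures by about one percentage point. For the secondary outcomes and the other work packages, the conclusion is only that their status should be labelled.

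**What to change.** In Data Analysis and in Sample Size:

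1. State that the between-arm difference in FMA at T4 (12 months) is the single primary test at two-sided 5%. This is the end of the one-year treatment and fits the stated long-term aim. In Sample Size, tie the 7-point difference and the SD of 11.6 to that visit.
2. Report the 3-, 6- and 9-month FMA differences as secondary estimates with confidence intervals.
3. Label the OCS, the Barthel Index, WP2 to WP7 and the biomarker correlations as secondary or exploratory, so that an isolated p < 0.05 is not read as confirmatory.

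The designation should be made before anyone sees FMA results by arm. The cost is a few sentences. The 88 evaluable and 97 enrolled patients in the Sample Size section do not change. The one loss is that an isolated early-visit difference can no longer support the primary claim.
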